## Abstract

**Background:**

Overweight and obesity result from excessive fat accumulation and pose significant global health challenges linked to various diseases. Recent research suggests that gut microbiota, particularly dysbiosis, is vital in obesity development. Next-generation probiotics, especially *Akkermansia muciniphila*, alongside compounds found in green tea extract and konjac glucomannan, offer promise in obesity management by enhancing gut microbiota balance and metabolic function. This research investigates a unique supplement that integrates these elements, proposing that it will outperform lifestyle changes alone in improving anthropometric measures, body composition, metabolic metrics, blood pressure, and appetite among overweight or obese adults.

**Methods:**

This study will include 72 overweight or obese patients, who will be randomly assigned to either the intervention or control group within a randomized, triple-blind controlled clinical trial. The intervention group will consume 2 g of beverage sachets containing pasteurized *Akkermansia muciniphila*, green tea extract, and konjac glucomannan three times daily. In comparison, the control group will take 2 g of microcrystalline cellulose three times daily for 8 weeks. Evaluations of anthropometry (body mass index, waist and hip circumference), body composition (fat mass, fat-free mass, total body water, etc.), appetite using a visual analogue scale, blood pressure, and biochemical parameters including fasting blood glucose (FBS), total cholesterol (TC), triglycerides (TG), low- and high-density lipoprotein (LDL and HDL) will be conducted.

**Discussion:**

The results of this study will provide evidence for the synergistic effects of *Akkermansia muciniphila* combined with prebiotics in the management of obesity and its associated metabolic states.

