### Objectives {7}

This study explores methods to prevent and manage obesity and its complications by examining a novel beverage powder supplement containing pasteurized *Akkermansia muciniphila*, green tea extract, and glucomannan konjac. Although the effects of each component have been previously investigated, the impact of combining these components has not been explored. The primary focus is on the supplement’s effects on body composition and anthropometric measurements, as well as metabolic parameters (including fasting blood glucose and serum lipid profile), blood pressure, and appetite, as secondary outcomes in overweight or obese adults. We hypothesize that this supplement, when combined with lifestyle interventions such as dietary therapy and physical activity, is more effective than lifestyle interventions alone in improving these outcome variables.

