### Trial design {8}

Our study will be a randomized, triple-blind, parallel-group, superiority trial with a 1:1 allocation ratio. Overweight and obese adults will be randomly assigned to either a new beverage powder supplement or a placebo for 8 weeks, along with standard lifestyle guidance. This design enables a thorough comparison of the supplement’s effectiveness against the placebo, while accounting for potential confounding variables through blinding and randomization.

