## Interventions

### Explanation for the choice of comparators {6b}

A placebo was chosen to isolate the effects of the supplement on the outcome variables. This approach enables a controlled evaluation of changes solely caused by the investigational supplement. The placebo will be given with identical appearance features to maintain participant blinding.

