### Intervention description {11a}

A hypocaloric diet (500 kcal deficit) consisting of 50% carbohydrates, 20% protein, and 30% fat will be prescribed for participants in both groups. Total energy expenditure will be calculated based on the Mifflin equation. Participants will be encouraged to engage in 150 min of physical activity per week.

This study will utilize a supplement consisting of pasteurized *Akkermansia muciniphila*, green tea extract, and glucomannan konjac, offered in 2-g sachets. The placebo is formulated with microcrystalline cellulose and also comes in 2-g sachets. Participants will be instructed to consume one sachet 30 min before every meal (breakfast, lunch, and dinner) for 8 weeks. Parsi Lact Company (Shiraz, Iran) prepared and packaged the supplements and placebos in sachet form. Both the placebo and the supplement exhibit the highest level of similarity, and the containers will remain unlabeled and coded as A or B to ensure both researchers and participants are unaware of the type of intervention they will receive. Each participant will receive a monthly supply of the sachets they need for consumption over the course of a month. To promote sachet consumption, participants will receive weekly calls and briefing messages. Compliance will be tracked by counting the monthly returned used and unused sachets. Additionally, we will assess sachet consumption through food recalls. At the beginning of the study, all participants will complete a checklist to collect their general characteristics, medical history, and information regarding medications and supplements they are currently using.

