## Discussion

Obesity and its related disorders present a significant public health challenge globally. In addition to traditional weight loss medications, next-generation probiotics (NGPs) appear to hold promise as a preventive and treatment measure against obesity [25]. Emerging research is investigating the benefits of next-generation probiotic supplements, with a focus on the effects of *Akkermansia muciniphila* on metabolic conditions such as obesity and diabetes.

Although *Akkermansia muciniphila* shows potential for treating obesity and type 2 diabetes (T2D), human research is scarce [26]. Further human studies could better clarify the preventive or therapeutic benefits of this promising next-generation probiotic.

Although studies have focused on the effectiveness of live or pasteurized *Akkermansia muciniphila,* the effect of this bacterium in combination with prebiotics has not yet been investigated. Filling this gap could result in innovative treatments for metabolic conditions, including obesity. The purpose of this study is to investigate the effect of a novel beverage containing pasteurized *Akkermansia muciniphila*, glucomannan, and green tea extract on body composition, anthropometric indices, metabolic markers, blood pressure, and appetite in adults with overweight or obesity. If the intervention shows favorable outcomes, it will represent a valuable step toward developing recombinant supplements with specific therapeutic targets.

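### The abstract promises evidence of synergy, but a two-arm trial of the full combination against placebo cannot estimate synergy or any component's effect

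*Protocol article*

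**What the plan says.** The abstract, under Discussion, tells the reader what the trial will contribute: "The results of this study will provide evidence for the synergistic effects of" *Akkermansia muciniphila* given with prebiotics.

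The design is set out in three places:

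- Trial design {8} describes a "randomized, triple-blind, parallel-group, superiority trial with a 1:1 allocation ratio", with participants "randomly assigned to either a new beverage powder supplement or a placebo for 8 weeks".
- Intervention description {11a} puts all three active components in one product (the bacterium with "green tea extract, and glucomannan konjac, offered in 2-g sachets"). It then says "The placebo is formulated with microcrystalline cellulose and also comes in 2-g sachets". Both groups get the same diet prescription and activity advice.
- Explanation for the choice of comparators {6b} says "A placebo was chosen to isolate the effects of the supplement on the outcome variables". That refers to the supplement as a whole.

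Objectives {7} hypothesises that the supplement plus lifestyle measures "is more effective than lifestyle interventions alone in improving these outcome variables". The main Discussion gives as the gap to be filled that "the effect of this bacterium in combination with prebiotics has not yet been investigated". Neither of these sections mentions synergy.

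**The concern.** Synergy is a statement about how the effect of a combination relates to the effects of its parts. This trial observes the combination and the absence of all parts, and nothing in between. The abstract therefore promises a conclusion that no result of the trial could support.

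The protocol itself supplies the rival explanation. Its Background section credits glucomannan with effects on obesity, satiety, lipids and blood pressure, and green tea extract with possible effects on weight, glucose, cholesterol and blood pressure. These overlap closely with the trial's outcomes. For the pasteurized bacterium alone, the same section reports only a slight fall from baseline in weight, fat mass and hip circumference. An effect due entirely to the fibre or the extract is plausible on this account, yet the abstract would have it read as an interaction with the bacterium.

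The abstract is the part most people read, and its framing can carry over into the report of results.

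**Working it through.** **The plan's own figure.** The protocol attaches no number to synergy. Its only sizing (Sample size {14}) is for a difference between two group means: standardized effect 0.80, power 0.90, α = 0.05, giving 27 per group. That figure reproduces with a one-sided α: 2 × ((1.645 + 1.282)/0.80)² = 26.8, rounded up to 27. With a two-sided α it would be 33, which is a separate matter. Either way, the calculation concerns the combination against placebo and has no component term.

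**What the two arms identify.** Let A, G and K indicate the bacterium, green tea extract and glucomannan. A full model for the mean outcome has 8 parameters: one intercept, three main effects (A, G, K), three two-way interactions (AG, AK, GK) and one three-way interaction (AGK).

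| Arm | Int. | A | G | K | AG | AK | GK | AGK |
|---|---|---|---|---|---|---|---|---|
| Placebo | 1 | 0 | 0 | 0 | 0 | 0 | 0 | 0 |
| Supplement | 1 | 1 | 1 | 1 | 1 | 1 | 1 | 1 |

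This matrix has rank 2 out of 8. The estimable quantities are the placebo mean and the single difference

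D = A + G + K + AG + AK + GK + AGK.

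No term on the right can be separated from the others. Treating the two prebiotics as one factor does not help. With b for the bacterium, p for the prebiotic mix and i for their interaction, the trial estimates D = b + p + i. The interaction contrast (both − bacterium only − mix only + neither) needs four cell means, and only two are observed.

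**What this means for a positive result.** Suppose the true difference equals the planning value, D = 0.80. Each of these states produces exactly that difference:

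- One active component: K = 0.80, everything else 0.
- Pure additivity: A = G = K = 0.80/3 = 0.267, no interaction.
- Pure synergy: all main effects 0, AGK = 0.80.
- Antagonism: A = G = K = 0.40, interactions summing to −0.40, so 1.20 − 0.40 = 0.80.

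The data have the same expectation under all four, so no test on these two arms can prefer one to another. More participants would narrow the interval for D and leave the ambiguity unchanged.

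**Indirect routes.** The between-group ANOVA or ANCOVA in Statistical methods {20a} has no component term, and no comparison with single-component studies is planned. The listed outcomes include no microbiota measure that might offer mechanistic support.

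**Scale of a design that could answer the question (illustration only).** Assume a 2×2 factorial, bacterium yes/no by prebiotic mix yes/no, with two-sided α = 0.05 and power 0.90. The interaction contrast has variance 4 × SD²/n with n per cell, so n = 4 × ((1.960 + 1.282)/δ)².

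| Assumed interaction δ (SD units) | n per cell | Total | Power with 72 in four cells of 18 |
|---|---|---|---|
| 0.80 | 66 | 264 | about 40% |
| 0.40 | 263 | 1052 | about 13% |

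Splitting the present 72 participants into four cells would therefore not rescue the claim either.

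**The case against.** The best reply is that this is one adjective in one sentence of an abstract. The operative sections (objectives, comparator rationale, analysis, main Discussion) all address the effect of the combined product, which the design can estimate. No hypothesis, outcome, sample size or test depends on synergy, and the word may be a loose way of saying combined. Evidence about the bacterium given together with prebiotics is a legitimate product of this trial, and how the main report will be worded is conjecture. It can also be said that the four-cell requirement belongs to one definition of synergy, departure from additivity. A weaker definition, the combination beating each component alone, would not necessarily need the no-treatment cell.

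Much of this stands as a limit on scope. The trial design section and the gap statement in the main Discussion contain no error and need no change. The planned comparison is valid, and the issue is one of interpretation.

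It does not remove the point. Under the weaker definition single-component arms are still required, and there are none. Reading the word loosely is also difficult, because the Background section sets out a specific interaction mechanism: a green tea catechin promotes growth of this bacterium, and glucose-based fibre may enhance that. After that rationale a reader will take the word literally, and nothing elsewhere in the article corrects it.

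**Conclusion.** The concern holds. The abstract assigns the trial a property that its design does not have. With two arms, 2 of 8 parameters are estimable, and neither an interaction nor a component effect can be recovered at any sample size. This rests only on the arms as described and on synergy meaning either more than additive or better than each component alone. It does not depend on effect sizes, variances or dropout. The factorial sample sizes do depend on the assumed interactions, and serve only to show that the question needs a different trial.

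The consequence is confined to what may be concluded. The supplement-versus-placebo comparison and the stated hypothesis are unaffected.

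**What to change.** Replace the sentence in the abstract's Discussion with wording such as: *The results will show whether the combined product, added to lifestyle advice, is superior to placebo; the contribution of each component and any synergy between them cannot be determined.* State the same limit in the conclusions of the main report, where a positive result should be attributed to the product as a whole.

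No procedure, outcome, analysis or sample size changes. The cost is a more modest claim. If synergy is of real interest, it belongs in a separate factorial trial with component arms.

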**Trial registration:**

Iranian Registry of Clinical Trials (IRCT20250222064807N2) (2025/03/26).

**Supplementary Information:**

The online version contains supplementary material available at 10.1186/s13063-025-09180-3.

## Introduction

### Background and rationale {6a}

Overweight and obesity are acknowledged as global health issues [1]. Obesity is defined as abnormal or excessive fat accumulation that may be harmful to health [2]. The World Health Organization (WHO) defines overweight individuals as those with a BMI between 25 and 29.9 kg/m^2^, whereas obesity is indicated by a BMI of 30 kg/m^2^ or more. Obesity is further divided into three classes: class I (BMI = 30–34.9 kg/m^2^), class II (35–39.9 kg/m^2^), and class III (≥ 40 kg/m^2^) [3]. Being obese heightens the risk of numerous diseases and conditions, which are associated with a higher risk of mortality. These include yype 2 diabetes mellitus (T2DM), cardiovascular diseases (CVD), metabolic syndrome (MetS), chronic kidney disease (CKD), elevated lipid levels, high blood pressure, nonalcoholic fatty liver disease (NAFLD), certain cancer types, obstructive sleep apnea, osteoarthritis, and depression [4]. Obesity rates are increasing globally, and managing this issue is difficult due to its complex etiology, which involves various contributing factors such as poor diets, lack of physical activity, genetic predispositions, and social and environmental influences [5].

Increasing evidence indicates that gut microbiota, an important environmental factor, has a considerable influence on the onset and advancement of obesity [6]. Dysbiosis—an imbalance in the microbiome—leads to increased appetite and the development of metabolic disorders, both of which contribute to obesity and its associated issues [7]. Probiotics are live microorganisms that provide health benefits when consumed in adequate amounts [8]. Probiotics are well-known for their ability to enhance gut microbiota and combat dysbiosis [9]. Probiotics influence obesity by effectively regulating the gut’s microbial balance, reducing insulin resistance, and improving feelings of fullness [7]. Although conventional probiotics tend to have limited beneficial effects, next-generation probiotics (NGP) are now recognized as innovative preventive and therapeutic options [10].

*Akkermansia muciniphila*, a bacterium that inhabits the mucus layer of the gastrointestinal tract, has emerged as a promising next-generation probiotic for addressing obesity-related conditions [11]. *A. muciniphila* affects obesity by regulating metabolism and energy balance while also improving insulin sensitivity and glucose control [12]. *A. muciniphila* has shown an inverse relationship with the development of inflammation, disrupted adipose tissue metabolism, and metabolic disorders in animal models of obesity [13]. Depommier et al. reported that pasteurized A. *muciniphila* improved insulin sensitivity and reduced serum insulin, total cholesterol, liver function, and inflammatory biomarkers in overweight or obese, insulin-resistant volunteers compared to placebo. It also led to a slight decrease in body weight, fat mass, and hip circumference from baseline, without significantly impacting the gut microbiome composition [14].

Green tea extract is rich in various polyphenolic compounds with antioxidant benefits. However, the key active ingredients are flavanol monomers called catechins, particularly epigallocatechin-3-gallate and epicatechin-3-gallate, which are the most potent antioxidant compounds [15]. Numerous laboratory studies have indicated that the polyphenols found in green tea might affect gut microbiota, hinting at possible anti-obesity effects through the modulation of gut bacteria [16].

EGCG has been demonstrated to modify gut microbiota by promoting the growth of A. *muciniphila*, which helps improve gut dysbiosis and enhances barrier integrity. A recent laboratory study revealed that when EGCG is co-metabolized with mucin and glucose, it boosts the growth of A. *muciniphila*, further supporting the proposed mechanisms of polyphenolic prebiotic effects. This effective co-metabolism implies that incorporating EGCG with glucose-based dietary fibers could significantly increase the levels of this bacterium within the intestinal microbiota [17]. Current research indicates that GTE might aid in weight control, blood glucose regulation, and lowering total cholesterol (TC), LDL cholesterol (LDL-C), and blood pressure (BP) in overweight or obese individuals [18].

Konjac glucomannan (KGM) is a hydrocolloidal polysaccharide fiber derived from the tubers of Amorphophallus konjac. KGM offers potential health benefits due to its diverse biological activities, which include anti-diabetic, anti-obesity, laxative, prebiotic, and anti-inflammatory effects [19]. KGM can help combat type 2 diabetes, reduce obesity, and lower blood pressure and lipid levels. Its hydration capacity and enhanced viscosity promote feelings of fullness, slow down glycemic responses, and limit lipid absorption. KGM helps prevent metabolic syndrome by regulating gut microbiota [20].

### Objectives {7}

This study explores methods to prevent and manage obesity and its complications by examining a novel beverage powder supplement containing pasteurized *Akkermansia muciniphila*, green tea extract, and glucomannan konjac. Although the effects of each component have been previously investigated, the impact of combining these components has not been explored. The primary focus is on the supplement’s effects on body composition and anthropometric measurements, as well as metabolic parameters (including fasting blood glucose and serum lipid profile), blood pressure, and appetite, as secondary outcomes in overweight or obese adults. We hypothesize that this supplement, when combined with lifestyle interventions such as dietary therapy and physical activity, is more effective than lifestyle interventions alone in improving these outcome variables.

### Trial design {8}

Our study will be a randomized, triple-blind, parallel-group, superiority trial with a 1:1 allocation ratio. Overweight and obese adults will be randomly assigned to either a new beverage powder supplement or a placebo for 8 weeks, along with standard lifestyle guidance. This design enables a thorough comparison of the supplement’s effectiveness against the placebo, while accounting for potential confounding variables through blinding and randomization.

## Methods: participants, interventions and outcomes

### Study setting {9}

This randomized, triple-blind, placebo-controlled clinical trial with a parallel-group design will take place over four months, starting in June 2025, in a nutrition clinic located in Mashhad, Iran.

### Eligibility criteria {10}

#### Inclusion criteria

Adults aged 18 to 45 who are overweight or obese, with a body mass index (BMI) ranging from 27 to 34.9 kg/m^2^, and waist circumference greater than 102 cm for men and greater than 88 cm for women, who maintain a stable weight (no more than 5% weight change in the last 3 months), and provide written consent, will be recruited from a nutrition clinic in Mashhad, Iran.

### Exclusion criteria

We will exclude individuals who are pregnant, lactating, or postmenopausal; professional athletes or individuals undergoing changes in the intensity and frequency of their physical activities throughout the last month; individuals with a confirmed clinical history of eating disorders, gastrointestinal diseases, cardiovascular, hepatic, renal, pulmonary, or endocrine diseases (such as thyroid conditions or diabetes), cancer, or any severe acute or chronic disease; current smokers, drug or alcohol addicts; those with known allergies or sensitivities to supplement or placebo components; individuals with a history of bariatric surgery; those who skip at least one meal; individuals on special diets, such as vegetarian diets; those with a regular intake of more than 300 mg of caffeine or more than 30 g of fiber per day; those adhering to a calorie-restricted diet for three months prior to the start of the study; individuals who routinely consume pre-, pro-, and synbiotic products; those who take antibiotics for one month before the study begins; or individuals using medications, including cholesterol and lipid-lowering drugs (e.g., statins), blood sugar-lowering drugs (e.g., insulin, metformin, liraglutide), antihypertensive medications, drugs affecting GI function, weight, body composition, or appetite (e.g., antipsychotics, corticosteroids, anti-obesity drugs, oral contraceptives, antidepressants), weight loss supplements (including those affecting appetite, metabolism, or food absorption) such as orlistat, and drugs interacting with green tea (e.g., digoxin, tacrolimus, warfarin).

Participants will be excluded from further analysis if they opt out, use antibiotics or other pre-, pro-, and synbiotic products, or meet the exclusion criteria anytime during the study, or do not comply with their assigned treatment regimen during the study.

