### Methods in analysis to handle protocol non-adherence and any statistical methods to handle missing data {20c}

All analyses will follow the intention-to-treat (ITT) principle. Missing data will be addressed using multiple imputation under the assumption of missing at random (MAR). Anthropometric measures, body composition variables, blood pressure, biochemical indices, and questionnaire scores will be included in the imputation model using a fully conditional specification (FCS) approach. In addition, sensitivity analyses will be performed with complete cases to confirm the robustness of the results.

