### Adverse event reporting and harms {22}

Participants will stay in contact with the researchers once a week, and any issues or adverse effects that arise during the intervention will be discussed. If any adverse side effects or problems are identified, participants will be removed from the study after consulting with the research team and specialists in the relevant field. We follow institutional guidelines for reporting and managing adverse effects.

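### The eligibility section drops randomised participants from analysis for events after randomisation, while the analysis section promises intention-to-treat throughout; nothing says which rule governs

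*Protocol article*

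**What the plan says.** Three parts of the protocol article bear on who is analysed.

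- **Exclusion criteria, last sentence.** "Participants will be excluded from further analysis if they opt out, use antibiotics or other pre-, pro-, and synbiotic products", and further if they "or meet the exclusion criteria anytime during the study, or do not comply with their assigned treatment regimen during the study". Each of these events can happen after randomisation.
- **Section {20c}, on non-adherence and missing data.** "All analyses will follow the intention-to-treat (ITT) principle". Missing values are to be multiply imputed assuming missing at random, with a complete-case sensitivity analysis. No per-protocol set is named.
- **Section {11c}, on adherence.** Missing more than 20% of doses leads to a counselling session. Exclusion from analysis is not mentioned, and no section defines the degree of non-compliance that triggers it.

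Three further sections describe stopping or leaving in different terms. Section {11b} stops the intervention. Section {5d} gives a participant with an intolerable adverse event the option to withdraw. Section {22} says "If any adverse side effects or problems are identified, participants will be removed from the study", with the qualification that this follows consultation with the team and specialists.

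**The concern.** A randomised participant who takes antibiotics or misses many sachets is deleted under one rule and kept under the other. The analysis set underlies every primary and secondary result, so this choice should not be open once data are in hand.

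Compliance, tolerability and opting out occur after randomisation and may depend on the product. The supplement contains a viscous fibre and green tea extract; section {11b} foresees gastrointestinal intolerance, and the protocol measures gastrointestinal symptoms with a rating scale. If those who tolerate the supplement poorly also respond less well, deleting them leaves a better-looking supplement arm. Imputation under {20c} does not help people who have been taken out of the data set. Because non-compliance has no threshold, who is removed would also rest on judgement.

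**Working it through.** **1. The two rules side by side.** The contradiction is textual and depends on no figure in the plan.

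| Event after randomisation | Exclusion criteria section | Section {20c} |
|---|---|---|
| Opts out | Excluded from analysis | Kept, outcome imputed if missing |
| Antibiotic or pre-/pro-/synbiotic use | Excluded | Kept |
| Meets an exclusion criterion on study | Excluded | Kept |
| Does not comply | Excluded | Kept |

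No section confines the first column to a secondary set or says which column prevails.

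**2. Size of the possible bias (assumed inputs).** From the protocol: 36 per group and a 20% dropout allowance (section {14}), and a two-sided 5% test (section {20a}). Assumed: no true effect; 20% removed per arm; removed supplement participants do δ worse than retained ones, with δ = 0.5, 0.8 or 1.0 SD; removed placebo participants do not differ from retained ones.

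The retained supplement mean then exceeds the mean of all randomised to that arm by 0.20 × δ.

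- Retained per arm: 36 × 0.80 = 28.8, taken as 29.
- Standard error of the difference: √(2/29) = 0.263 SD.
- Type I error: P(|Z + bias/0.263| > 1.96).

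| δ (SD) | Bias = 0.20 × δ (SD) | Type I error |
|---|---|---|
| 0.5 | 0.10 | 6.7% |
| 0.8 | 0.16 | 9.3% |
| 1.0 | 0.20 | 11.9% |

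**3. Dependence on the fraction excluded.** A simulation with 36 per arm, no true effect and 20,000 runs per setting used a different selection model. Supplement-arm exclusion was correlated with poor outcome (correlation 0.3 to 0.5) and placebo-arm exclusion was random.

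| Excluded per arm | Shift (SD) | Type I error |
|---|---|---|
| 10% | 0.06-0.10 | 5.4-6.6% |
| 20% | 0.11-0.18 | 6.8-10.2% |
| 25% | 0.13-0.21 | 7.6-12.3% |

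The two approaches agree in order of magnitude, and at 10% the inflation is slight.

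**4. Power.** At the protocol's standardised effect of 0.80, two-sided 5%, normal approximation, power is 92.4% with 36 analysed per group and 86.1% with 29. The first figure is an upper bound for intention-to-treat, because imputation does not restore all the information lost with missing outcomes.

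**The case against.** The best defence is that {20c} is the section devoted to non-adherence and missing data, that it speaks of all analyses, and that it would therefore govern. If so, nobody is deleted and there is no bias from this source. That is a possible outcome, but the protocol does not state it, and the exclusion sentence is just as categorical. Reading that sentence as withdrawal from follow-up does not fit either: it speaks of analysis, and a non-complier or antibiotic user can still be measured at week 8.

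The objection to the magnitude stands. The 20% is a dropout allowance, not a rate of exclusion for non-compliance or antibiotics. People without week-8 data lack outcomes under either rule, and imputation under missing at random need not remove bias from outcome-dependent dropout. The added harm falls mainly on those who are measured and then deleted, a fraction that is unknown and may be well below 20%.

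Four stronger readings are tempting and are not supported:

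- **That the comparison is biased.** This needs the exclusion rule to be applied and exclusions to depend on arm and outcome. Neither is established.
- **That section {22} deletes everyone with an adverse effect from the analysis.** It concerns removal from the study, after consultation. Such people become missing data, which {20c} would impute.
- **That the complete-case analysis would be the same selected set.** Under {20c}, a non-complier measured at week 8 is a complete case and is included.
- **That participants who follow the trial's own advice would be excluded.** The protocol says "Participants will be encouraged to engage in 150 min of physical activity per week" and lists as an exclusion "individuals undergoing changes in the intensity and frequency of their physical activities throughout the last month". That criterion is most naturally a look-back at screening, and applying it to participants who take the prescribed activity strains the text.

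**Conclusion.** The protocol contradicts itself on the analysis set, and this must be settled before analysis begins. Following the exclusion sentence would give a per-protocol comparison under an intention-to-treat label.

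Bias is a conditional risk, and its direction is not fixed by the documents. The 0.10-0.20 SD shift and the 7-12% type I error are an upper-end scenario: they rest on 20% removed per arm, outcome-related removal in the supplement arm only, and a gap of 0.5 to 1.0 SD between removed and retained. The contradiction stands without them.

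**What to change.** Replace the last sentence of the Exclusion criteria section with wording limited to the analysis set, for example: *All randomised participants are analysed in their assigned group, regardless of compliance, use of prohibited products or stopping the sachets.* It should not say that the exclusion criteria cease to matter after screening, since some of them bear on clinical management (pregnancy, interacting drugs). Clinical stopping decisions stay as they are.

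Then:

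- State that the end-of-study measurements already scheduled will be sought from participants who stop the sachets, unless they withdraw consent.
- Keep the present exclusions only as a labelled per-protocol sensitivity analysis, with non-compliance defined in advance. The 20% missed-dose figure in {11c} triggers counselling only. Using it as the cut-off would be a new choice for the sponsor to make.
- Reconcile the stop, withdraw and remove wording of {11b}, {5d} and {22}, so that stopping the intervention is distinguished from leaving the study.

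The cost is a protocol amendment, which section {25} requires the ethics committee to approve before implementation, and the effort of retaining people who stop the sachets. Recruitment began in June 2025 and was expected to end in October 2025, so the change should be dated and made before unblinding. The statistical downside is a possibly more diluted estimate of effect.
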